## Abstract

**Background:**

Respiratory distress syndrome is the main cause of mortality and morbidity in preterm infants. “Less invasive surfactant administration” (LISA), which describes intratracheal surfactant administration to spontaneously breathing infants via a small diameter tube, is recommended as the first-line treatment in preterm infants with more than 30% supplemental oxygen. Prophylactic use of LISA in preterm infants with less than 30% supplemental oxygen was not tested in randomised controlled trials yet, and long-term outcome data of the procedure are scarce.

**Methods:**

Preterm infants with a gestational age between 25 weeks + 0 days and 28 weeks + 6 days who are breathing spontaneously on continuous positive airway pressure with supplemental oxygen at or below 30% in the first hour of life will be randomised to a prophylactic LISA treatment with 100–200 mg surfactant intratracheally per kilogramme bodyweight (intervention group) or will continue the continuous positive airway pressure treatment (control group). Participants will have follow-up until age 5 years. At that time, the children will be tested by spirometry, and forced expiratory volume within 1-s *z*-scores will be compared between the intervention and control groups as the primary outcome parameter of the trial. Secondary endpoints include additional lung function parameters, endurance, motor development, intelligence, and sensitivity for infectious lung diseases. Short-term safety assessment will be done after completed enrolment (*n* = 698) and discharge of all infants. This safety assessment will include in-hospital mortality and short-term complications.

**Discussion:**

Robust data concerning the possible long-term benefits of prophylactic LISA treatment are lacking. The current observational data from the German Neonatal Network indicate that approximately 50% of preterm infants with supplemental oxygen at or below 30% within the first hour of life are treated with LISA. The pro.LISA trial will provide short- and long-term outcomes of preterm infants receiving prophylactic treatment and will clarify if prophylactic treatment should be given to all preterm infants or if the current practice of selective treatment if supplemental oxygen exceeds 30% is more appropriate.

**Trial registration:**

German Clinical Trials Register DRKS00028086. Prospectively registered on 8 February 2022.

## Administrative information

Note: The numbers in curly brackets in this protocol refer to the SPIRIT checklist item numbers. The order of the items has been modified to group similar items (see http://www.equator-network.org/reporting-guidelines/spirit-2013-statement-defining-standard-protocol-items-for-clinical-trials/).

## Introduction

### Background and rationale {6a}

Less invasive surfactant administration (LISA) describes intratracheal surfactant administration via a small diameter tube to spontaneously breathing infants [1]. The current guidelines recommend surfactant therapy in preterm infants if the fraction of inspired oxygen (FiO_2_) is higher than 0.30 and LISA as the optimal mode of administration for preterm infants on continuous positive airway pressure (CPAP) [2]. This recommendation is based on a number of randomised controlled trials and meta-analyses [3–7]. The use of prophylactic LISA in infants with FiO_2_ at or below 0.30 was not yet tested in randomised controlled trials.

Observational data from the GNN indicate that in infants with gestational age 25–28 weeks and FiO_2_ ≤ 0.30, LISA treatment rates are as high as 50%. Reasons for this high rate of LISA despite the lack of data and high costs of surfactant therapy are unclear.

Prophylactic surfactant therapy via an endotracheal tube is not superior to early CPAP and selective surfactant treatment of infants requiring intubation [8]. Furthermore, even LISA causes some stress for preterm infants, since the trachea is intubated with a small diameter tube, which can induce discomfort, coughing, desaturations, tracheal obstruction, and bradycardia. Possible benefits of LISA prophylaxis include a lower rate of intubation and mechanical ventilation and better long-term lung function [9]. The existing uncertainties concerning LISA prophylaxis prompted us to design and initiate the pro.LISA trial.

### Objectives {7}

The primary hypothesis of the pro.LISA study is that there is a difference in forced expiratory volume within 1 s (FEV_1_) at the age of 5 years between the intervention group (infants receiving prophylactic surfactant via LISA) and the control group (no prophylactic surfactant via LISA). Secondary hypotheses are that there are differences with respect to other lung function parameters, endurance, motor development, intelligence, and susceptibility to infectious lung disease.

### Trial design {8}

The pro.LISA study is a prospective, randomised, controlled, parallel-group, single-blinded, multicentre, national trial. Patients will be assigned in a 50:50% ratio to the intervention and control groups. The purpose of the trial is to show the superiority of the intervention with regard to the primary endpoint.

## Methods: participants, interventions, and outcomes

### Study setting {9}

Neonatal intensive care units in Germany are enrolled as participating sites. A list of participating centres is given in the “Acknowledgements” section.

### Eligibility criteria {10}

The following are the inclusion criteria:Preterm infants with gestational age between 25 weeks and 0 days and 28 weeks and 6 daysAge < 60 minSpontaneous breathingPulse oximetric measured oxygen saturation ≥ 90% at FiO_2_ ≤ 0.30Written informed consent of at least one legal guardian

The following is the exclusion criteria:Lethal malformations

### Who will take informed consent? {26a}

Pregnant women who are admitted to a centre participating in the pro.LISA trial with threatening preterm delivery before 29 weeks of gestation will be approached. Both parents/legal guardians will be asked for consent before enrolment. In case of an emergency situation (e.g. emergency C-section), the consent of only one parent is sufficient for enrolment. The other parent will be approached as soon as possible. Informed consent will be taken by qualified staff members of the participating site.

### Additional consent provisions for collection and use of participant data and biological specimens {26b}

Parents/legal guardians give consent for the collection and analysis of data to study the safety and efficacy of prophylactic LISA treatment. This includes the use of data for regulatory purposes and ancillary analyses (e.g. meta-analyses). All sites of the pro.LISA trial are part of the German Neonatal Network (GNN). In the GNN, deoxyribonucleic acid samples of participating children are collected. Parents are asked for separate consent for enrolment in the GNN.

### Interventions

#### Explanation for the choice of comparators {6b}

For preterm infants breathing spontaneously on CPAP, surfactant therapy if FiO_2_ exceeds 0.30 is recommended by the current guidelines [2] and was chosen as the control group procedure. In the intervention group, preterm infants will be treated with prophylactic LISA surfactant regardless of FiO_2_ in the first hour of life. We expect that approximately 50% of control group infants will develop FiO_2_ exceeding 0.30 within the first 3 days of life and will therefore be treated with LISA. If similar rates of additional LISA administrations within the first 3 days of life will be necessary in the intervention group will be analysed in the pro.LISA trial.

#### Intervention description {11a}

##### Intervention group

A small diameter tube (according to local standards) is placed via laryngoscopy in the trachea of the infant. Surfactant (100–200 mg/kg body weight) is administered while the baby is breathing spontaneously. Thereafter, the small diameter tube is removed and CPAP with positive end-expiratory pressure level of at least 6 cm H_2_O is continued. The intervention takes about 1 to 3 min.

##### Control group

In the control group, CPAP with a positive end-expiratory pressure level of at least 6 cm H_2_O is continued. LISA is only given if FiO_2_ increases to more than 30% or if the responsible physician observes respiratory distress of the infant.

#### Criteria for discontinuing or modifying allocated interventions {11b}

The intervention (prophylactic surfactant) will be applied immediately after enrolment. No criteria for modifications were defined.

#### Strategies to improve adherence to interventions {11c}

Interventions are documented in the intervention and control groups immediately after randomisation. Due to the short timeframe for the intervention, and the intensive care setting, no strategies to improve adherence were defined.

#### Relevant concomitant care permitted or prohibited during the trial {11d}

The only prohibited therapy is prophylactic surfactant in the control group.

#### Provisions for post-trial care {30}

Patients who are enrolled in the study are covered by patient insurance (Newline Group).

### Outcomes {12}

The primary endpoint of this study is FEV_1_ at the age of 5 years determined by spirometry and adjusted for age, sex, height, and ethnicity according to Global Lung Function Initiative standards (FEV_1_
*z*-scores) [10]. Analysis of the primary endpoint will be done by comparing the intervention and control groups of the full analysis set. Secondary efficacy endpoints at the age of 5 years are as follows:FVC *z*-score according to [10]FEV_1_/FVC *z*-score according to [10]Length in metres of running track in 3-min running test according to [11]Cerebral palsy defined as Gross Motor Function Classification System value > 1Score in Movement Assessment Battery for ChildrenIntelligence assessed by Wechsler Preschool and Primary Scale of Intelligence (WPPSI) IVObstructive bronchitis (treated with inhaled or other drugs) in the last 12 months

Spirometry measures (FEV_1_, FVC, and FEV_1_/FVC-scores) and the length of the running track will be aggregated as mean values. Movement Assessment Battery for Children and WPPSI-IV-scores will be aggregated as median scores. Cerebral palsy and obstructive bronchitis will be analysed as proportions. Safety endpoints will be assessed at discharge from the hospital and at the age of 5 years and include death and complications of premature birth. All adverse events and serious adverse events will be reported.

The following safety endpoints will be assessed at discharge from the hospital:DeathIntraventricular haemorrhage (IVH, each grade)IVH grade III or IVPeriventricular leukomalacia (PVL)Abdominal operation due to focal intestinal perforation (FIP)Abdominal operation due to necrotising enterocolitis (NEC)Laser surgery, cryocoagulation, or anti-VEGF treatment of retinopathy of prematurity (ROP)Operation due to a persistent ductus arteriosus (PDA)PneumothoraxBronchopulmonary dysplasia (BPD, need of O_2_ or breathing assistance with 36 weeks p.m.)Death or BPDDuration of mechanical ventilation (in days)Duration for need of O_2_ (in days)Duration of need of any breathing assistance (ventilation or CPAP) (in days)Mechanical ventilation during stay in hospitalMechanical ventilation during the first 72 h of lifeHerniotomyAbdominal operation due to other reasonsLung bleeding where transfusion or intubation is requiredBody weightBody lengthOne of the endpoints in 1–10.

The following safety endpoints will be assessed at the age of 5 years:General healthDevelopment compared to children of the same ageSystolic blood pressure (1st measurement)Systolic blood pressure (2nd measurement)Medium blood pressure (1st measurement)Medium blood pressure (2nd measurement)Diastolic blood pressure (1st measurement)Diastolic blood pressure (2nd measurement)Heart rateBreathing rateSpO_2_Systolic blood pressure after running testDiastolic blood pressure after running testMedium arterial pressure (MAD) after running testHeart rate after running testBreathing rate after running testSpO_2_ after running test

Safety endpoints will be compared in the safety analysis dataset. The method of aggregation for safety endpoints until discharge will be proportions for numbers 1–11, 15–19, and 22 and median values for 12–14 and 20–21. The method for aggregation of data at 5-year follow-up will be proportions for items 1–2 and mean values for all other endpoints. All statistical analyses are described in detail in the statistical analysis plan, which will be finalised before the randomisation of the last patient in the study.

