### Sample size {14}

The clinical aim is to detect a mean difference in FEV_1_
*z*-scores of 0.3 at the age of 5 years [9]. Based on the values of the GNN study, the *z*-score standard deviation is expected to be 1.07. The significance level alpha is set to 0.05 (two-sided) and power to 0.8. To detect this effect using a two-sample *t*-test, it requires data from 201 patients per group. The total sample size is calculated on the following assumptions: adjustment for multiple births (10%), rate of patients dying before discharge (2%), loss to follow-up rate (28%), and the rate of patients who will not be able to accomplish lung function tests at the age of 5 years (10%). Based on these estimates, we calculated that data from 349 patients per group are needed (698 patients in total, nQuery 7.0).

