#### Dissemination plans {31a}

In general, results from the study will only be published after the database has been closed. Exceptions are publications concerning the design of the study and descriptive results of safety analysis after discharge from the hospital of all enrolled infants. The latter is planned, since the primary endpoint will be measured 5 years after discharge of the last enrolled patient. Since short-term complications might be different between the groups, we are planning descriptive outcome analyses of these data after enrolment is completed.

The final report of the trial will be published within a period of 360 days upon completion of the study.

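### The median is the only stated summary for ventilation days; it reads 0 versus 0 if fewer than half of each arm is ventilated, and then hides any difference in ventilation burden

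*Protocol article*

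**What the plan says.** Protocol article, Outcomes {12}, lists 22 safety endpoints at hospital discharge. Counting through the list, number 12 is the duration of mechanical ventilation in days, number 15 is any ventilation during the hospital stay, and number 16 is ventilation in the first 72 hours. The same section sets the summary measures: "median values for 12–14 and 20–21", and "proportions for numbers 1–11, 15–19, and 22". Ventilation days are therefore summarised by a median, and both yes/no ventilation endpoints by proportions.

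Three other statements bear on the point:

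- Background and rationale {6a} names the hoped-for benefit: "Possible benefits of LISA prophylaxis include a lower rate of intubation and mechanical ventilation and better long-term lung function".
- Explanation for the choice of comparators {6b} says: "We expect that approximately 50% of control group infants will develop FiO_2_ exceeding 0.30 within the first 3 days of life". This describes oxygen need and later LISA, not ventilation. No ventilation rate is given anywhere in the article.
- On analysis, Outcomes {12} says "All statistical analyses are described in detail in the statistical analysis plan". Dissemination plans {31a} says of the short-term complications that "we are planning descriptive outcome analyses of these data after enrolment is completed".

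**The concern.** An infant who is never ventilated contributes 0 days. Once such infants make up more than half of an arm, that arm's median is 0, and it stays 0 however long the remaining infants are ventilated. If this holds in both arms, the report reads 0 versus 0 days whether prophylaxis shortens ventilation, lengthens it or does nothing.

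Endpoint 12 has a place beside endpoints 15 and 16 only because it carries something they do not: how much ventilation there was, as opposed to how many infants had any. The short-term report will appear years before the FEV1 result and is planned as descriptive, so the summary measure is largely the result itself. The article's Discussion also expects the trial to inform whether short-term benefits outweigh the stress, discomfort and cost of the procedure. Ventilation burden belongs in that weighing.

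**Working it through.** **Inputs from the article.** 349 infants per arm (Sample size {14}); median for endpoint 12; proportions for endpoints 15 and 16.

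**Assumptions, because the article gives no figures.** The share ever ventilated in each arm, varied below. Days among ventilated infants are log-normal with median 5 and log-SD 1.1, rounded up to whole days.

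**Reproducing the plan's own figure.** There is none for ventilation. The 349 reproduces: a two-sample t-test for a difference of 0.3 with SD 1.07, two-sided alpha 0.05 and power 0.8 needs 201 per group, and 201 × 1.10 / (0.98 × 0.72 × 0.90) = 348.2, rounded up to 349.

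**Step 1: when is the median 0?** With 349 infants the median is the 175th ordered value. It exceeds 0 only if at least 175 infants were ventilated, so P(median > 0) = P(Binomial(349, p) ≥ 175). This does not depend on the assumed durations.

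| Share ventilated p | P(median > 0) |
|---|---|
| 30% | 0.000 |
| 40% | 0.0001 |
| 45% | 0.03 |
| 48% | 0.23 |
| 50% | 0.50 |
| 55% | 0.97 |
| 60% | 1.00 |

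**Step 2: both medians 0.** Multiply the two arms' probabilities of a zero median:

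- 45% vs 35%: 0.97 × 1.00 = 0.97
- 40% vs 30%: 0.9999 × 1.00 ≈ 1.00
- 55% vs 45%: 0.03 × 0.97 ≈ 0.03

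Simulation with 2,000 trials per scenario agrees: 0.97, 1.00 and 0.02.

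**Step 3: does the trial lose the lower rate of ventilation?** No. The planned proportions, compared with 349 per arm, have power 0.86 (30% vs 20%), 0.79 (40% vs 30%), 0.77 (45% vs 35%) and 0.75 (55% vs 45%).

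**Step 4: is anything lost?** Hold the ventilated share equal in both arms and shorten the median duration among ventilated infants from 5 to 3 days. The mean among ventilated infants is about median × exp(1.1²/2) + 0.5, the 0.5 allowing for rounding up: 5 × 1.831 + 0.5 = 9.66 days against 3 × 1.831 + 0.5 = 5.99. Ventilation days fall by 1 − 5.99/9.66 = 38%. Per infant this is 0.40 × 3.67 = 1.47 days at 40% ventilated, or 0.30 × 3.67 = 1.10 days at 30%. Both medians are 0 in practically every trial, and endpoint 15 does not move because the shares are equal. No stated ventilation summary shows the change.

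**Step 5: what would a mean per infant show?** The second moment among ventilated infants is about median² × exp(2 × 1.1²): 25 × 11.25 = 281 and 9 × 11.25 = 101, ignoring rounding. The variance per infant is p times the second moment, minus the squared mean.

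- Equal shares of 40%: (0.40 × 281 − 3.66²) + (0.40 × 101 − 2.20²) = 99 + 36 = 135. SE = √(135/349) = 0.62. The expected interval is 1.47 ± 1.22 days.
- 40% vs 30%, same durations: the difference is 0.10 × 9.66 = 0.97. The variances are 99 + (0.30 × 281 − 2.75²) = 99 + 77 = 176. SE = √(176/349) = 0.71. The expected interval is 0.97 ± 1.39 days.

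The mean shows the burden effect, but with a wide interval.

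**The case against.** The case against is substantial, and most of it limits the point.

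**The expected benefit is covered.** A reader might infer that the trial cannot show its main short-term benefit. The article does not support that. The benefit it names is a lower rate of intubation and ventilation, and endpoints 15 and 16 report ventilation as proportions with reasonable power (Step 3). This stands.

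**The condition is not established.** A reader might also take the 50% in section {6b} as showing that fewer than half will be ventilated. That figure concerns oxygen need in the first 3 days, whereas endpoint 12 has no 72-hour limit. Infants of 25 to 28 weeks may be ventilated later for other reasons, and the article's own list includes abdominal, ductal and hernia operations and lung bleeding. Entry on spontaneous breathing with FiO2 at or below 0.30 makes a share below half plausible, no more. At 55% or above the median is almost surely above 0. This stands too.

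**A summary is not a test.** Tests are left to the SAP, which is not shown, so the lack of one here is no fault. A rank test on the same days has power of about 0.77 at 40% vs 30% although both medians are 0. This is correct, but there the whole effect is in the share ventilated, which endpoint 15 already reports. With equal shares of 40% and duration cut from 5 to 3 days, the rank statistic shifts by 0.40² × (Φ(ln(5/3)/(1.1√2)) − 0.5) = 0.16 × 0.129 = 0.021. Its null SE with ties is √(699/(12 × 349²) × (1 − 0.6³)) = 0.019, so power is about 1 − Φ(1.96 − 1.07) = 0.19. A p-value beside 0 versus 0 would also give no size of effect.

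**The median is a usual choice for skewed durations, and the mean is noisy.** This is true, and it argues for adding the mean, not for removing the median.

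**Conclusion.** The point holds in a limited form and is minor. The article fixes a summary for endpoint 12 that carries no information about ventilation burden if fewer than half of the infants in each arm are ventilated. That condition is an assumption. Both medians are 0 in about 97% of trials at 45% versus 35%, in practically all at 40% versus 30% or lower, and in about 3% at 55% versus 45%. These probabilities depend only on the share ventilated and on 349 per arm. The sizes of the burden effects also rest on the assumed log-normal durations, and the standard errors ignore correlation within families.

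Two stronger conclusions do not follow: that the trial is blind to its expected short-term benefit, and that the median must go. The first fails because of endpoints 15 and 16, the second because the alternative has its own weakness. Endpoint 12 is one of 22 discharge safety endpoints in a descriptive report. The primary endpoint, its test and the sample size are unaffected.

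**What to change.** In Outcomes {12} and the SAP, keep the median for endpoint 12 and print the quartiles with it. Add the mean number of ventilation days per infant in the safety set, counting 0 for infants never ventilated. Give the between-group difference with a bootstrap interval that resamples families, so that siblings from multiple births stay together.

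Quartiles alone are not enough: by the same reasoning as for the median, the upper quartile is 0 in any arm with fewer than a quarter ventilated. Days among ventilated infants only should not be relied on for the comparison, because being ventilated is itself an event after randomisation that treatment may change.

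The cost is a sentence in each document and a short piece of code. No new data are needed, and the article leaves the SAP open until shortly before the last patient is included. The downside is that a few infants ventilated for very long can move the mean. Under the assumptions above the interval is roughly ±1.2 to ±1.4 days, so the mean should be read as an estimate of burden beside the median and the proportions, not as a decisive comparison.

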### Participant timeline {13}

**Table Tabb:** 

	In hospital					After discharge (years)				
	Before birth until 60 min	< 60 min	72–84 h	36 weeks p.m	Discharge	1	2	3	4	5
Eligibility screen	x									
Informed consent	x									
Allocation		x								
Intervention group: prophylactic surfactant immediately after allocation		x								
Control group: no prophylactic surfactant after allocation		x								
Baseline assessment	x									
Outcome assessment (safety)			x	x	x	x	x	x	x	x
Adverse events		x	x		x					
Outcome assessment (efficacy)										x

